#### Secondary analysis

Secondary analysis is based on the comparisons of secondary outcomes between the allopurinol and mannitol-placebo group, both for the total study population and separately for subgroups of CCHD. Additionally, a secondary analysis will be performed to assess an interaction with gender, as females possibly benefit more from allopurinol administration than males [30]. Descriptive statistics will be applied, including the independent sample *t*-test or the Mann-Whitney *U*-test for continuous data and Pearson’s chi-square test for categorical data. Safety analyses will be based on incidences of (serious) adverse events in both groups.

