#### Sample size

The sample size is calculated based on an assumed reduction in (absolute) incidence of 20% in the more prevalent subgroup of prenatal diagnosis (± 80% of the total population, control event rate assumed 71%) and a reduction of 9% in the postnatal diagnosis group (± 20% of the population, control event rate assumed 55%). With a total sample size of 236 CCHD neonates, of which 188 in the prenatal subgroup and 48 in the postnatal subgroup, the study has approximately 80% power to demonstrate the advantage of allopurinol in the total group with a two-sided alpha of 5%. The power of the hierarchical testing strategy is only slightly affected, given the large proportion of the prenatal group (80%). The effect sizes are a relevant and viable expectation and are based on the results of previous neuroprotective studies on head cooling in neonatal encephalopathy and perioperative allopurinol administration in CCHD neonates [26, 59]. RStudio version 3.6.1 was used for the sample size analysis.

Participants will be substituted in the following cases: (1) when cardiac surgery with CPB in the first month of life is unexpectedly not required or (2) when there is consent withdrawal before postoperative MRI. It is to be expected that these cases rarely occur.

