### Safety

An independent DMC with extensive clinical research experience will evaluate the safety and efficacy data at regular intervals and advise on the results of the planned interim analysis. This DMC consists of a pediatric neurologist, pediatric intensivist, pediatric cardiologist, and a clinical epidemiologist. The study team will screen the medical records of participants daily to identify any adverse events. In addition, we will instruct the parents/legal guardians to contact the study team if adverse events occur during the follow-up period of 24 months. The nature, severity, and causal relationship with the study medication of each adverse event occurring during the trial will be evaluated. All details, such as duration, clinical symptoms, treatment, and outcome of the event, are recorded by the study team on case report forms. The Medical Dictionary for Regulatory Activities Terminology will be used for the coding of adverse events. Unexpected serious adverse events will be reported to the Medical Research Ethical Committee and DMC. It is known that CCHD and cardiac surgery itself can result in several adverse events. Therefore, expected disease-related events will be recorded on separate case report forms, which are presented in Additional file 2. The safety analysis will include all CCHD neonates, including subjects who withdraw from participation during the study. However, we will only collect their safety data from the period that they participated in the study. In trial publications, we will include all unexpected and expected adverse events that are significantly more present in the allopurinol group compared to the mannitol-placebo group. Further details are described in a DMC charter, which is available upon request from the corresponding author.

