#### Risk and benefit assessment

The investigational medicinal products will be studied in neonates with CCHD at high risk of brain injury. CCHD neonates are vulnerable patients who are unable to give consent themselves and are potentially at risk for drug interactions and adverse events of allopurinol. However, the need for pharmacological neuroprotection strategies in this neonatal CCHD population is evident. Previous data suggesting neuro- and cardioprotective effects of neonatal allopurinol doses of 20 mg/kg with low risk of severe side effects should be verified in a large, well-designed trial to prove efficacy or futility. As this trial is placebo-controlled, half of the CCHD neonates will not have a potential beneficial effect of allopurinol. Nevertheless, the use of a placebo agent seems justifiable as study participants often benefit from participating in a randomized controlled trial, considering the potential benefit for future CCHD neonates, and the fact that mannitol-placebo PFI 20 mg/kg is safe [38, 62]. Care is taken to ensure that the study-driven burden for all participants is kept to a minimum.

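### The rule for publishing adverse events is a one-directional significance filter, so small to moderate excesses, serious events without a significant difference, and events commoner on placebo could go unpublished

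*Protocol article*

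**What the plan says.** The Safety section of the protocol article sets the criterion for what enters trial publications: "we will include all unexpected and expected adverse events that are significantly more present in the allopurinol group compared to the mannitol-placebo group". The criterion has two parts, statistical significance and direction (excess on allopurinol), and it covers expected and unexpected events alike.

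The same section describes recording, coding, causality assessment, regular review by the data monitoring committee, and reporting of unexpected serious events to the ethics committee and the data monitoring committee. None of these depends on significance.

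Two other places touch the subject. Under Secondary analysis, "Safety analyses will be based on incidences of (serious) adverse events in both groups"; this concerns analysis, not publication. Results and dissemination promises registry posting and journal publication of the final results but does not say what adverse-event data they will contain.

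**The concern.** A significance test is a poor gate for harms. The trial is sized for a large effect on a common composite outcome, so tests on less common adverse events, or on smaller differences, have low power. A true excess that misses the threshold by chance would fall outside the stated publication criterion. So would a serious event seen a few times in one arm, and any event more frequent on placebo, which might be evidence of benefit.

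The Abstract names safety as a secondary outcome, and the Conclusions make standard use conditional on allopurinol proving beneficial and safe. If published harms were selected by p-value and direction, readers could not see the full balance between the arms or pool those events with other trials.

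**Working it through.** **Inputs from the protocol article**

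- Sample size: "With a total sample size of 236 CCHD neonates, of which 188 in the prenatal subgroup and 48 in the postnatal subgroup" (Sample size).
- Allocation: "half of the CCHD neonates will not have a potential beneficial effect of allopurinol" (Risk and benefit assessment), so 236 / 2 = 118 per arm.
- Test: the Secondary analysis section names "Pearson’s chi-square test for categorical data". For a 2×2 table this equals the two-sided pooled Z-test.
- Design rates (Sample size): 71% falling by 20 points in the prenatal group, and 55% falling by 9 points in the postnatal group.

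**Assumptions.** The document gives no rates, significance level or multiplicity rule for adverse events. I assume a two-sided 5% level, the chi-square test and a range of illustrative rates. Any multiplicity adjustment would lower the chances below.

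**Step 1: reproduce the plan's own figure.** The weighted rates are:

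- Control: (188 × 0.71 + 48 × 0.55) / 236 = 0.6775
- Allopurinol: (188 × 0.51 + 48 × 0.46) / 236 = 0.4998

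With n per arm, difference d, mean rate p̄ and arm rates p₁ and p₂:

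power = Φ{ [d − 1.96·√(2p̄(1−p̄)/n)] / √([p₁(1−p₁) + p₂(1−p₂)]/n) }

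With n = 118: Φ{(0.1776 − 0.1256) / 0.0630} = Φ(0.826) = 79.6%. This agrees with the stated power of approximately 80%.

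**Step 2: apply the same test to adverse events.** For 5% v 10% the formula gives Φ{(0.05 − 0.0672) / 0.0341} = Φ(−0.504) = 30.7%. Because the normal approximation is rough at low rates, the table uses the exact binomial distribution of the chi-square/Z-test, except for 2% v 5%, where simulation gave 21.5% and exact enumeration the same rounded 22%. Only results significant in the direction of excess on allopurinol are counted in the exact figures.

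| True rate, placebo v allopurinol | Passes the filter | Fisher's exact test instead |
|---|---|---|
| 1% v 2% | 7% | 1% |
| 2% v 4% | 13% | 6% |
| 2% v 5% | 22% | not computed |
| 5% v 10% | 32% | 22% |
| 10% v 15% | 21% | 16% |
| 20% v 30% | 43% | 37% |
| 30% v 40% | 36% | 32% |
| 10% v 20% | 58% | 51% |
| 5% v 15% | 76% | 66% |
| 20% v 40% | 93% | 90% |

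**Step 3: excess needed for an 80% chance of passing** (normal approximation): from 2% to about 11%, from 5% to 16%, from 10% to 24%, from 20% to 36%, and from 30% to 48%.

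**Step 4: observed counts that would fail.** With 118 per arm, z = (difference in proportions) / √(2p̄(1−p̄)/118), and 1.96 is needed.

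- 0 v 3 neonates: 0.0254 / 0.0146 = 1.74
- 2 v 8 neonates: 0.0508 / 0.0262 = 1.94
- 5 v 12 neonates: 0.0593 / 0.0337 = 1.76

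All three patterns, each with more events on allopurinol, fall outside the criterion.

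**The case against.** The sentence guarantees that certain events will be included. It does not say that all others are left out, and the word *only* is not there. That is correct, so exclusion is an inference. It remains the natural reading: a criterion naming significant excesses would have little purpose if every event were published anyway, and no other section widens it. The commitment to analyse incidences in both arms carries no filter, but it does not promise publication.

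A second objection is that the gravest harms largely bypass the rule. Death within one month, being too unstable for MRI, and moderate or severe brain injury form the primary outcome. Seizure activity, cardiac function, cerebral oxygenation, neurodevelopment and length of stay are secondary outcomes compared by arm. This stands, and it narrows the point to other adverse events and to deaths after the first month.

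A reader might also infer that most real harms would go unreported. The documents do not support that. *Most* depends on rates and effect sizes that the document does not give, and it fails for larger excesses, including 10% v 20%. *Unreported* is too strong, because committee review, ethics-committee reporting and registry posting remain, although the registry content is not specified. Nor does any section say that non-significance will be presented as absence of harm, or make published safety data a basis for market registration; the Discussion ties that application to a beneficial effect in the total and prenatal groups.

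**Conclusion.** The concern holds in a limited form and should be fixed. The stated publication criterion for adverse events is significance in one direction, and nothing else in the document commits the trial to publishing the rest. Small to moderate excesses would often be missing from publications. Under the assumptions in the working, excesses of up to 5 points at the tabulated control rates of 1% to 10%, and 10-point excesses at control rates of 20% to 30%, pass in 7% to 43% of trials. A 10% v 20% excess passes in 58%, and large excesses usually pass. Events more frequent on placebo never meet the criterion.

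These figures rest on 118 per arm, a two-sided 5% chi-square test and illustrative rates. The defect lies in publication. Data collection, safety oversight, the primary test and the outcomes compared by arm are untouched.

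**What to change.** Replace the sentence in the Safety section with a commitment to publish all serious and non-serious adverse events, expected and unexpected, by arm. For each, give the number of neonates affected, the denominator, the risk difference and its 95% confidence interval, regardless of p-value or direction. A frequency floor for non-serious events is acceptable; a significance filter is not.

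The cost is one sentence and a supplementary table. The Safety section already provides for the events to be recorded and coded, so no new data collection and no change to trial conduct is needed.

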### Blinding

The study team, care providers, parents, and assessors of neurodevelopmental outcomes are blinded to the allocation in the trial (quadruple blinding). Blinding of the study team will be maintained throughout the inclusion period and until all CCHD neonates underwent primary outcome assessment. This can be secured as allopurinol PFI has an identical appearance as mannitol-placebo PFI. Blinding of parents, care providers, and assessors of neurodevelopmental outcomes will be continued until all follow-up visits at 24 months are completed. The following parties are unblinded during the trial: (1) Ace Pharmaceuticals, for randomization, preparation, and labeling of study medication; (2) UMC Utrecht Pharmacy, operating as a central distributor of study medication to all study sites; (3) an independent laboratory, to analyze the pharmacokinetic data; and (4) the DMC, if it requests full unblinding to arrive at a recommendation. An independent statistician will prepare the DMC reports and planned interim analysis by group level (A vs. B) and will not be aware of the actual treatment assignment. Premature unblinding by opening an “emergency breaking code envelope” of a specific CCHD neonate may take place when knowledge of the study medication arm is necessary for adequate treatment of a (serious) adverse event.

### Ethical considerations

#### Regulatory aspects

The trial (EudraCT 2017-004596-31; ClinicalTrials.gov NCT04217421) will be conducted according to the principles of the Helsinki Declaration (2013). The trial is approved by the Medical Research Ethical Committee of the UMC Utrecht (reference number NL62772.041.18) and the Dutch competent authority “Centrale Commissie Mensgebonden Onderzoek” (reference number NL62772.041.18). Protocol modifications will be submitted to these trial regulators for approval and will be communicated with all relevant parties, e.g., participants, study sites, and trial registries.

#### Recruitment and consent

Parents of neonates with a prenatal diagnosis of CCHD are informed about the study by the obstetrician and/or fetal cardiologist between 24 and 36 weeks of gestation and are asked for written consent before the start of delivery. Parents of neonates with a postnatal diagnosis of CCHD are informed about the trial by the pediatric cardiologist shortly after the diagnosis and have to give written consent at least 24 h before cardiac surgery. The information letter and consent form are provided in Additional file 3.

#### Risk and benefit assessment

The investigational medicinal products will be studied in neonates with CCHD at high risk of brain injury. CCHD neonates are vulnerable patients who are unable to give consent themselves and are potentially at risk for drug interactions and adverse events of allopurinol. However, the need for pharmacological neuroprotection strategies in this neonatal CCHD population is evident. Previous data suggesting neuro- and cardioprotective effects of neonatal allopurinol doses of 20 mg/kg with low risk of severe side effects should be verified in a large, well-designed trial to prove efficacy or futility. As this trial is placebo-controlled, half of the CCHD neonates will not have a potential beneficial effect of allopurinol. Nevertheless, the use of a placebo agent seems justifiable as study participants often benefit from participating in a randomized controlled trial, considering the potential benefit for future CCHD neonates, and the fact that mannitol-placebo PFI 20 mg/kg is safe [38, 62]. Care is taken to ensure that the study-driven burden for all participants is kept to a minimum.

#### Provisions for post-trial care

Post-trial care is deemed not to be necessary for this trial. Participants will not receive compensation for trial participation. The sponsor has an insurance, following legal requirements for clinical research in the Netherlands, that provides cover for damage to research subjects through injury or death caused by study procedures. The insurance applies to the damage that occurs during the trial or within 4 years after trial termination.

### Results and dissemination

The final trial results will be posted on the registration page of ClinicalTrials.gov and presented via publication in scientific journals. Additionally, the results will be communicated to the parents or legal guardians of study participants. An individual or group that substantially contributed to the conception, design, acquisition, analysis, or interpretation of the trial will be granted authorship, provided that they also contribute to the drafting of the manuscript or critically revise the manuscript. We do not intend to use professional writers.

#### *Ancillary studies*

On the consent form, parents or legal guardians are asked for permission to share participant data and maternal data within the European Association Brain in Congenital Heart Disease (EU-ABC) research consortium that currently consists of the UMC Utrecht, University Children’s Hospital Zurich, University Hospital Giessen, German Heart Center Munich, and King’s College Hospital London. Future research using the data generated in this trial might include studies investigating the effect of allopurinol on neurodevelopmental outcomes after 24 months.

## Discussion

The CRUCIAL trial focuses on the neuro- and cardioprotective effects of allopurinol administration early after birth and around cardiac surgery with CPB in neonates with CCHD. We aim to provide definite answers on allopurinol’s immediate effects on brain injury and cardiac function, as well as late effects on neurodevelopment. If allopurinol proves to be beneficial in limiting parenchymal brain injury, our subsequent goal is to make allopurinol clinically available for all CCHD neonates.

Large randomized controlled trials that include both structural brain imaging with MRI and long-term follow-up are needed to investigate the effects of neuroprotective drugs in CCHD neonates. A phase III, randomized, quadruple-blinded, placebo-controlled, multicenter study is the most adequate design to prove the efficacy or futility of allopurinol as a neuroprotective agent in the CCHD population. A phase III study seems justifiable since previous studies have already suggested neurocardiac protective effects of allopurinol without serious side effects [24–26]. Multiple pediatric heart centers should be involved to include our anticipated sample size of CCHD neonates considering the relatively low prevalence of CCHD and the heterogeneity of cardiac defects [1]. An interim analysis halfway with the option to stop for efficacy or futility ensures that allopurinol is not unethically withheld or unnecessary given to subsequent CCHD neonates [61].

Today in the Netherlands, most neonates are diagnosed with CCHD before birth (approximately 80%) due to improvements in prenatal diagnostics over the past years [8]. As the proportion of CCHD neonates with a prenatal diagnosis is expected to further increase in the following years, this is the primary subgroup of interest in our trial. This group will receive allopurinol or mannitol-placebo early postnatally and perioperatively [63]. As the subgroup of CCHD neonates with a postnatal diagnosis (approximately 20%) can be considered to be at even higher risk for brain lesions (as they often are admitted to the intensive care unit with respiratory and circulatory insufficiency), these patients will also be included in this trial, although study medication can only be given perioperatively in this group [34]. The total group (*n* = 236) and subgroup of CCHD neonates with a prenatal diagnosis (*n* = 188) will be primarily analyzed and the postnatal diagnosis subgroup (*n* = 48) secondarily. A beneficial effect of allopurinol in both the total and prenatal group will be required to apply for market registration and to make allopurinol available for all CCHD neonates, including those with a postnatal diagnosis.

The brain of neonates with CCHD is at high risk for parenchymal injury, especially ischemic lesions such as white matter injury and stroke [8]. Since we now know that brain injury mainly occurs in the vulnerable periods early after birth and around cardiac surgery with CPB, this offers opportunities for investigating the effects of neuroprotective drugs in the CCHD population within a clear time frame [19]. By administering and reaching target levels of allopurinol before potential cerebral hypoxic-ischemic events occur, this “pre-treatment” maximizes the chance of success in reducing parenchymal brain lesions [64].

Dosage and timing of allopurinol administration (20 mg/kg) are based on previous pharmacokinetic and clinical studies performed in neonates who underwent cardiac surgery and neonates with perinatal asphyxia [26–29, 54]. XO inhibition by allopurinol, reducing the production of ROS, was reached with 5–10 mg/kg in neonates with hypoplastic left heart syndrome and with 10 mg/kg (and 20 mg/kg priming dose) in neonates who underwent extracorporeal membrane oxygenation [32, 33]. High dosages of allopurinol seem to have additional neuroprotective properties as this increases scavenging of ROS and chelation of non-protein bound iron, without increasing the risk of severe adverse effects [21, 22, 27]. Previously, 2 doses of allopurinol 20 mg/kg in a 12-h interval postnatally led to improved long-term neurodevelopmental outcomes in neonates with moderate asphyxia [65]. However, in CCHD neonates, renal function should be taken into account as allopurinol is entirely cleared by the kidneys and acute kidney injury could temporarily occur after cardiac surgery with CPB [20]. Therefore, the postoperative dose will be administered 24 h (instead of 12 h) after surgery. Additionally, a pharmacokinetic substudy will be performed in the first 24 patients to monitor the levels of allopurinol directly after birth and around cardiac surgery with CPB.

We chose to include brain injury on postoperative MRI in the composite primary outcome instead of neurodevelopmental outcome at the age of 24 months. Firstly, neonatal MRI can be used as a “bridging biomarker” for long-term outcomes since ischemic white matter lesions are known to be associated with lower intelligence quotient and attention problems at school-age, and in case of posterior limb internal capsule involvement, also motor problems [36]. Consequently, the beneficial effects of allopurinol on parenchymal brain lesions are expected to improve long-term neurodevelopmental outcomes. Furthermore, early neurodevelopmental outcome at the age of 24 months seems less predictive for long-term outcomes, since CCHD neonates “grow into their deficits” and neurodevelopmental problems become more apparent at school-age [4]. Moreover, CCHD neonates with a syndromic disorder (approximately 15%) can be included as well by assessing brain injury postoperatively on MRI (as part of the composite primary outcome) instead of neurodevelopmental outcome at the age of 24 months. This syndromic CCHD subgroup is expected to score lower on neurodevelopmental outcomes and, therefore, will be analyzed separately [58]. Lastly, as many CCHD neonates undergo multi-staged cardiac repair through infancy, neurodevelopmental outcomes may exhibit a collective effect from multiple surgeries.

